### Discontinuation of intervention

The study intervention will be discontinued if any of the following exclusion criteria is present:
Tracheostomy for other reason than acute respiratory insufficiencyFacial surgery with contraindication to NIVPulmonary cancer needing surgeryPulmonary transplantationPulmonary volume reduction (by surgery, valves or coils)

Furthermore, participants may withdraw from the study without any reason and the investigator might temporarily or permanently withdraw a participant from the study for any safety reason or in the participant’s best interests.

### Adverse event reporting

All adverse events (serious and non-serious) will be recorded in the AE pages of the eCRF. The investigator will assess the seriousness of each adverse event and will thoroughly document serious adverse events, including a definitive medical diagnosis, if possible. The investigator will furthermore assess the intensity (mild, moderate, severe) as well as causal relationship (according to WHO-UMC) between AEs and the study interventions. AEs will be followed up until resolution or stabilization at an acceptable level.

Serious adverse events will additionally be notified to the sponsor without delay, except for those defined by the protocol and investigators brochure as not requiring notification. The notification will be followed by a written report describing the course of the event and providing additional information, as well as any additional anonymized documents. The sponsor will then report all SAEs that are both unexpected and reasonably related to the study intervention to Health Authorities and Ethics Committees of involved countries in accordance with international and local regulations. The sponsor will report all safety information from the trial in the Annual Safety Reports.

### Data management and protection

Data recorded in the eCRF will be identified by a patient number and initials (first letter of last name and first letter of first name). No directly nominative data will be collected and all data sent to the sponsor will be anonymized before transfer.

In accordance with the GCP, the sponsor will ensure data quality by data monitoring and auditing. The persons responsible for these tasks will take all necessary precautions to ensure confidentiality and are bound by professional secrecy. All participants will have agreed to the access of their personal data for quality control in writing.

### Data processing

The eCRF has been developed by CLINFILE. Data will be entered via a secured web interface and stored on a secured platform. Data will be processed in accordance with the provisions of Regulation (EU) 2016/679 (General Data Protection Regulation).

Data will not be shared with third parties, but only between investigators and La Fondation du Souffle.

### Calculation of sample size

With an expected 1-year admission-free survival of 35% in the control group and 55% in the home NIV groups, an accrual period of 2 years, and a minimum follow-up of 12 months, 93 patients in each group are required to provide the study a power of 80% to detect a difference between the control group and each of the three NIV groups, with a familywise error rate (FWER) of 5%. Sample size was estimated by simulations of 200 trials with SAS Version 9.4.

### Statistical analysis

All analyses will be performed on the intent-to-treat (all randomized patients) and total (including non-randomized screen-failures) populations.

All analyses will be performed on the intent-to-treat and total populations. With the exception of the statistical analysis of the primary endpoint, all statistical tests will be performed at the 5% significant level (two-sided formulation).

If applicable, missing data will be taken into account using multiple imputations.

#### Primary endpoint: admission-free survival

Admission-free survival is defined as the time from randomization to hospital admission or death. Each comparison will be done with a two-sided log-rank test.

#### Secondary endpoints: superiority of home NIV

The superiority of any of the three home NIV strategies over the hospital-based NIV in terms of:
Global survivalExacerbation frequencyArterial partial pressure of carbon dioxide (PaCO2) and arterial partial pressure of oxygen (PaO2)QoL (Charlson, Severe Respiratory Insufficiency Questionnaire score, St George’s Respiratory Questionnaire score, EuroQol, Medical Research Council dyspnea score, Epworth sleepiness score, Pittsburgh score, CAT score, SF36, EQ 5D5L questionnaire)DyspneaCosts managementSerious adverse events (SAEs) occurrence frequency

Analyses will be based on a three-step Bonferroni-based chain procedure. With this procedure, the familywise error rate (FWER) will be controlled.

In the first step, nocturnal NIV and nocturnal NIV with high monitoring will be compared with the control group. Tests will be performed at the two-sided 0.025 level. If no test is significant, no further comparison will be made. If at least one comparison is significant, the rescue NIV group will be compared with the control group at the 0.025 level if only one test was significant at step 1 or at the 0.05 level if both tests were significant. If the comparison between the control group and the rescue NIV group is performed at the 0.025 level and is significant, the not significant comparison at step 1 will be re-tested at the 0.05 level [18].

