#### Secondary objectives

The secondary objectives of the study are to demonstrate for severe COPD patients after an episode of acute respiratory insufficiency with hypoventilation, that any of the three home NIV strategies are superior to standard no-home NIV in terms of:
Global survivalExacerbations frequencyComorbidityQuestionnaires (quality of life, sleep, and dyspnea)(Serious) adverse event (AEs and SAEs) occurrence rateCost-effectiveness

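### As printed, the superiority chain also governs SAEs and overall survival, so the rescue arm's formal harm comparison with control can depend on results in the other two arms

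*Protocol article*

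**What the plan says.** All references are to the protocol article.

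- **Secondary objectives.** The aim is to show that "any of the three home NIV strategies are superior to standard no-home NIV in terms of" a list that includes global survival and the rate of AEs and SAEs.
- **Secondary endpoints: superiority of home NIV** (statistical part). The outcome list begins with global survival and ends with SAE frequency. General AEs are not on it. The text continues: "Analyses will be based on a three-step Bonferroni-based chain procedure".
- **Step 1 of the chain.** "In the first step, nocturnal NIV and nocturnal NIV with high monitoring will be compared with the control group". The level is given as "Tests will be performed at the two-sided 0.025 level". Rescue NIV is not in this step.
- **The gate.** "If no test is significant, no further comparison will be made". Otherwise: "If at least one comparison is significant, the rescue NIV group will be compared with the control group at the 0.025 level" when one step-1 test succeeded, or at 0.05 when both did.
- **Statistical analysis** (general part). "With the exception of the statistical analysis of the primary endpoint, all statistical tests will be performed at the 5% significant level", two-sided.
- **Primary endpoint: admission-free survival** (statistical part). A two-sided log-rank test for each comparison, with no multiplicity rule.
- **Calculation of sample size.** 93 per group for 80% power for control against each of the three NIV groups, with a familywise error rate of 5%.

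**The concern.** A gatekeeping chain limits false claims of benefit. For harm it works the other way: it withholds a comparison that could show a problem. Whether rescue NIV causes excess SAEs or deaths does not depend on whether the two other arms differ from control, yet the printed text makes the rescue comparison wait for that.

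The stop rule is stated under a heading whose list includes both outcomes, so this is not a detail left open for an analysis plan. An analyst who followed that section literally could report SAEs and survival for the rescue arm without any formal comparison with control. The article also names no specific DSMB, so no independent board is identified that would make the comparison.

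The article does not speak with one voice, however. The general Statistical analysis section gives a different rule for the same outcomes.

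**Working it through.** **1. Which endpoint does the chain fit?** Inputs from Calculation of sample size: 1-year admission-free survival of 35% (control) and 55% (each NIV arm), 2-year accrual, at least 12 months of follow-up, 93 per arm. Assumptions added: exponential survival, uniform accrual, follow-up of 12 to 36 months, no dropout.

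- Hazard ratio = ln(0.55) / ln(0.35) = 0.569.
- Log-rank tests put through the printed chain, 4,000 simulated trials: the three comparisons succeed in about 89%, 90% and 87% of trials, and all three together in 80.2%.

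The stated 80% is reproduced as the power to win all three comparisons under this chain. That suggests the chain is the primary endpoint's procedure, printed under the secondary heading. It is not proof, because some simpler formulas also come close to 93 (Freedman at 0.05/3 gives about 92 per arm).

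**2. How often is the gate closed if it runs on each outcome?** If both nocturnal arms share the control rate, their two test statistics have correlation 0.5, because they share one control group of equal size. The two-sided 0.025 critical value is 2.241.

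- P(neither step-1 test significant) = P(|Z1| < 2.241 and |Z2| < 2.241) = about 0.954.

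So rescue would go formally untested in about 95% of such trials, whatever its own event rate.

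**3. Illustration for SAEs.** The article gives no SAE rates, so those below are assumptions. Test: z = (p_arm − p_control) / √(2p̄(1 − p̄)/n), with n = 93, chain levels as printed, 200,000 simulated trials. The ungated comparison is a two-sided 5% test.

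| Control / nocturnal / rescue | Gate opens | Rescue excess declared, chain | Ungated |
|---|---|---|---|
| 10% / 10% / 25% | 4.4% | 2.6% | 78.2% |
| 10% / 10% / 30% | – | 3.4% | 94.0% |
| 10% / 15% / 25% | about 18% | 17% | about 78% |

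Hand check of the ungated figure for 10% against 25%: p̄ = 0.175; null SE = √(2 × 0.175 × 0.825 / 93) = 0.0557; alternative SE = √((0.09 + 0.1875) / 93) = 0.0546; power = Φ((0.15 − 1.96 × 0.0557) / 0.0546) = Φ(0.75) = about 0.77. The chain figure cannot exceed the gate's 4.4%.

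At the planned 100 per arm, 10% / 10% / 25% gives about 2.8% under the chain and 82% ungated.

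**4. Illustration for death.** Assumed 1-year mortality is 30% in the other three arms, with 100 per arm. Rescue mortality of 40%, 45% or 50% is declared different in 2.4%, 2.6% or 4.1% of trials under the chain, against 47%, 79% or 96% ungated.

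**5. If the gate runs once, on the primary endpoint.** Under the design assumptions it opens in about 95% of trials, so the chain figures in steps 3 and 4 do not apply. If no NIV arm differs from control on the primary endpoint, it opens in about 4.4%.

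**The case against.** The strongest reply is that the article's general rule already provides the comparison. The Statistical analysis section reserves special treatment for the primary endpoint and tests everything else at 5%. Together with the sample-size match, this suggests misplaced text: once the chain is moved to the primary endpoint, the gating of SAEs and survival disappears. This largely stands, and it is why the point is put as a contradiction with a consequence, not as a settled plan to withhold safety tests. It does not remove the point. The general rule fixes a significance level and does not say which comparisons are made, whereas the specific section does.

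Other parts of the reply also stand:

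- The section does not say that the gate runs separately for each outcome. That is an inference.
- A reader might infer that harm in the rescue arm would go unseen. The documents do not support that. Adverse event reporting requires all AEs and SAEs to be recorded, with causality assessment and safety reporting, whatever any test shows. Secondary endpoints includes AE frequency at set times, SAEs and Kaplan-Meier overall survival. The stop rule limits formal comparisons, not recording, tabulation or estimation by arm.
- The 3% figure needs harm confined to the rescue arm. Many of the listed SAEs relate to NIV itself and could be shared by all three NIV arms. Shared harm opens the two-sided gate more often, as the 15% row shows.

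That safety detail is commonly left to the full protocol or analysis plan is true, but it does not answer a stop rule that the article itself states.

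**Conclusion.** The point holds in a limited form. As printed, SAE frequency and global survival fall under the chain. If the chain is run on each outcome, the rescue arm's formal comparison with control depends on a significant result in a nocturnal arm. The same article gives a conflicting 5% rule for all non-primary tests, and the chain most likely belongs to the primary endpoint.

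Under the per-outcome reading the effect is large when harm is specific to rescue: about 3% against 78% detection at the assumed 10% / 10% / 25%. It narrows when the nocturnal arms share some of the harm: about 17% against 78% with those arms at 15%. All event rates are assumptions.

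The documents do not support the stronger conclusion that the rescue arm would have no safety data or no safety reporting, or that the gating is the settled plan. What could be lost is the formal between-arm harm comparison for one of the three strategies. The text should be corrected because the change is cheap and the literal reading works badly for harm.

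**What to change.** 1. Reconcile the Statistical analysis section, the primary endpoint section and the secondary superiority section on where the chain applies. If it is the primary endpoint's procedure, print it there. If it also covers secondary efficacy outcomes, say whether the gate runs per outcome or once, and amend the general 5% statement to match.
2. State in the secondary superiority section that SAEs and all-cause death, read for harm, are outside the gate. Compare each of the three home NIV arms with control whatever the other arms show, as a difference or ratio with a 95% confidence interval labelled as not adjusted for multiplicity.
3. Keep the chain for efficacy superiority claims only. A claim of superior survival can still go through it.

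The cost is a few sentences of protocol or analysis-plan wording, with no new data, staff or patients. The downside is a somewhat higher chance of a false safety signal in one arm, which the labelling makes plain.

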#### Secondary endpoint: cost-effectiveness

Cost-effectiveness analysis will be analyzed as cost per avoided admission, including:
Equipment costsMaintenance and support costs for the home NIVMedical, nursing, and support staffHospital admissions

Economic evaluation of home-based NIV in patients with severe COPD based on (1) the 4-arm comparison and (2) the international population, following the recommendations from the French national health authority and the CHEERS statement [19, 20].

### Insurance

The sponsor has taken out insurance for the full study period, covering its own civil liability and that of any agent (doctor or research staff). The sponsor will also provide full compensation for any damages caused by the study to the study participants and their beneficiaries, unless the sponsor can prove that the harm is not the fault of the sponsor or any agent. Compensation cannot be refused on the grounds of a third party act or the voluntary withdrawal of the person who initially consented to participate in the study.

### Steering committee

Composed of 5 members (the 3 national coordinating investigators: Profs. [name], [name], [name]; the biostatistician [name]; and the sponsor’s representative, [name]), this committee defined the overall structure of the study and determined the initial methodology. It coordinates information and oversees the study including follow-up on termination and removal rules by monthly email exchange and conference calls upon demand.

### Data Safety Monitoring Board (DSMB)

This study has no specific DSMB as the pharmacovigilance for this type of study is managed locally. The oversight of the data, conduct and progress of the study are performed by the steering committee.

### Audits and inspections

An audit can be carried out at any time by independent persons appointed by the sponsor or the competent authority. The aim of the audits is to ensure the quality of the study, the validity of the results, and compliance with the legislation and regulations in force. The persons leading and monitoring the study agree to comply with the sponsor’s requirements and with the competent authority regarding study audits or inspections. The audit may encompass all stages of the study, from the development of the protocol to the publication of the results and the storage of the data used or produced as part of the study.

## Discussion

Despite COPD being the principal indication of home NIV [21], only three [10, 15, 16] out of six [6–8, 10, 15, 16] randomized controlled studies have shown the benefit of home ventilation. This contradiction leads to completely different rates of implementation of this treatment in different countries with, for example, 1% of COPD patients receiving home NIV in New Zealand [22] and 49% of COPD patients receiving this treatment in Hong Kong [12].

R2M is a novel study on home NIV in COPD patients with the aim to resolve this paradox.

The main objective of this study is to answer the question, if the quality of nocturnal NIV might be responsible for the negative results. This will be achieved by providing a group of patients with extensive monitoring and personalized (targeted) ventilation settings. This entails the major limitation of this study: the risk of providing a treatment based on exceptional expert care which might not be routinely feasible and in all cases.

Furthermore, R2M will investigate the comorbidities typical for COPD patients, such as cardiac insufficiency, OSA, or associated asthma, which might influence ventilation outcomes. To this end, cardiac ultrasound, spirometry, and polysomnography will be performed upon inclusion and before randomization. These extensive evaluations during the 15 days between inclusion and randomization of patients are relatively burdensome, but these examinations are usually routinely recommended.

Additionally, R2M will record the reasons for non-inclusion of patients by a dedicated page in the eCRF, in order to evaluate the percentage of ventilated COPD patients that are screening failures. Indeed, the three studies that have demonstrated the benefit of home ventilation for survival had significant recruiting difficulties with up to 94% of screening failure [10, 15, 16].

The GOLD 2017 document already indicates home NIV to be of some use for a selected group of patients [17], and long-term home non-invasive ventilation (NIV), specifically adapted to the patients “phenotype”, is supposed to improve the prognosis for COPD patients who remain persistently hypercapnic. Therefore, considering the impact of COPD on the patient’s quality of life and life expectancy [12, 13] as well as the GBD [1, 2], the R2M study remains of significant importance despite its relative constraints.

### Trial status

This study is running in France since 09/05/2019 with the first patient having been recruited on 04/07/2019 and an inclusion period of 24 months. The study has equally been submitted in Spain and Portugal on 10/09/2019 and 22/07/2019, respectively. The current version of the protocol is version 4.0, dated May 28, 2019.

## Data Availability

The owner of the data is the sponsor, La Fondation du Souffle. The data cannot be used or disclosed to a third party without its prior permission and upon analysis of the demand of the scientific committee of la Foundation du Souffle. Results of the study will be disseminated in the final report, scientific publications, and in the context of scientific congresses.

## Abbreviations

ABG: Arterial blood gases
AHI: Apnea/hypopnea index
AHRF: Acute hypercapnic respiratory failure (AHRF),
BMI: Body mass index
BTS: British Thoracic Society
CAT: COPD Assessment Test
CE: Conformité Européenne (European Conformity)
CPAP: Continuous positive airway pressure
COPD: Chronic obstructive pulmonary disease
ESS: Epworth Sleepiness Scale
FEV1: Forced expiratory volume in 1 s
FVC: Forced vital capacity
FWER: Familywise error rate
GBD: Global burden of disease
GCP: Good Clinical Practice
GOLD: Global Initiative for Chronic Obstructive Lung Disease
HDU: High-dependency unit
ICU: Intensive care unit
ISO: International Organization for Standardization
MMRC: Modified Medical Research Council
NIV: Non-invasive ventilation
OSA: Obstructive sleep apnea
OSAHS: Obstructive sleep apnea hypopnea syndrome
QoL: Quality of life
QoS: Quality of sleep
SAE: Serious adverse event
SAQoL: Stroke and Aphasia Quality of Life
SRIQ: Severe Respiratory Insufficiency Questionnaire
